### Blinding

Outcome measures taken at baseline, post-PR and follow-up will be taken by a researcher blinded to group allocation. It is not possible to blind participants to treatment due to the nature of a PR intervention. Research staff will be blinded to outcome measures. Participants will be advised not to reveal their group during the follow-up assessments. Episodes of un-blinding will be documented and reported for both time points.

#### Qualitative data collection

All interview and focus group discussions will be audio-recorded, expected to last on average 20–40 min and will be conducted by a trained interviewer. Recordings will be transcribed verbatim, with identifiable information removed. Consent will be obtained from participants prior to their involvement. PR deliverers will be invited to participate in in-depth interviews at the end of the study to discuss aspects of PR, such as insights into barriers to attendance, logistical barriers of running a PR programme and their views of patients’ experiences of the intervention.

### Book of testimonies and evaluation form

Participants within PR will be asked to log their experience of PR as they progress through the programme. This will be in the form of a PR log book accessible to participants before, during and after sessions as well as a dedicated evaluation form (Appendix B). Staff involved in PR will also receive the same evaluation form at the end of the study.

#### Quantitative data collection

Baseline characteristics will comprise patient sociodemographics (age, sex), age of leaving full-time education, anthropometrics (height, weight, body mass index), smoking status and pack years, biomass fuel exposure, primary respiratory diagnosis, secondary respiratory diagnosis (if appropriate), spirometry data (postbronchodilation forced expiratory volume in 1 s (FEV_1_), postbronchodilation Forced Vital Capacity (FVC) and FEV_1_/FVC ratio) (EasyOne Plus spirometer, NDD Medical Technologies, Switzerland); number of hospitalisations in the last 12 months, comorbidities, treatment and previous participation in PR. The height will be measured by stadiometer and the weight will be measured by electronic scales.

### Outcomes

A schedule of events is provided in table 1 and measures are in accordance with the recommended minimum data set for PR in LMIC.^16^ In the case of a face-to-face follow-up, appointment at 12-week postbaseline cannot be conducted, questionnaires will be collected over telephone.

**Table 1 T1:** Schedule of events

	Baseline	6 weeks	12 weeks	
	Face-to-face	Face-to-face	Face-to-face	Telephone*
Sociodemographics	x			
Age of leaving full time education	x			
Smoking and biomass exposure	x			
Respiratory diagnoses	x			
Spirometry	x			
Hospitalisations in the last 12 months	x			
Comorbidities	x			
Treatments	x			
Physical activity monitoring	x	x		
Anthropometrics	x	x	x	
ISWT and ESWT	x	x	x	
5x sit to stand	x	x	x	
MRC score	x	x	x	x
EQ5D score	x	x	x	x
Pain scores for chest pain	x	x	x	x
CCQ	x	x	x	x
CAT	x	x	x	x
HADS	x	x	x	x
WPAI questionnaire	x	x	x	x

CAT, COPD Assessment Test; CCQ, Clinical COPD Questionnaire score; ESWT, Endurance Shuttle Walk Test; HADS, Hospital Anxiety and Depression Scale; ISWT, Incremental Shuttle Walk Test; MRC, Medical Research Council; WPAI, Work Productivity and Activity Impairment Questionnaire.

#### Primary outcome

The primary outcome of exercise capacity will be measured using the ISWT.^21^ The ISWT will require patients to walk up and down a 10-metre course marked out using cones at walking speeds dictated by an audio signal played on an audio device. Each participant will receive standardised instructions to: ‘Walk at a steady pace, aiming to turn around when you hear the signal. You should continue to walk until you feel that you are unable to maintain the required speed without becoming unduly breathless’. To account for any learning effect, a practice ISWT will be performed and the greatest distance walked from either test will be taken forward. The test will be terminated when either: (1) the patient indicates that they are unable to continue, (2) the operator determines that the patient is not fit to continue or (3) the operator assesses that the patient was unable to sustain the speed and cover the distance to the cone prior to the beep sounding.

#### Secondary outcomes

##### Exercise capacity and muscular strength

Participants will be asked to complete a five repetition sit to stand test,^24^ as an indication of lower extremity strength. The time taken for participants to complete this task will be recorded.

The endurance shuttle walk test is a constant load walking test, in which a participant is required to walk at 85% of their maximal ISWT walking speed. An audio signal is played to the participant and they are required to walk around a 10-metre course marked by cones.^22^

##### Symptoms

The MRC Dyspnoea Scale will be used to assess dyspnoea.^25^ This is a 5-point questionnaire, in which the participant self-reports their dyspnoea. Chest pain will be assessed using four questions based on Brief Pain Inventory (Short Form).^26^

##### Quality of life

The Clinical COPD Questionnaire^27^ is a 10-item health-related quality of life questionnaire that is divided into three domains: symptoms, functional and mental. The COPD assessment test (CAT)^28^ is a self-administered questionnaire that is used to quantify the symptom burden of COPD. The questionnaire consists of eight items, each with a 6-point scale, creating a total score out of 40. The EQ5D5L^29^ will be used to assess generic health-related quality of life and comprises of five dimensions: mobility, self-care, usual activities, pain/discomfort and anxiety/depression. The questionnaire also contains a visual analogue scale, where the participant identifies their health from ‘the best you can imagine’ and the ‘worst you can imagine’.

##### Psychological well-being

The self-reported Hospital Anxiety and Depression Scale^30^ will be used to determine levels of anxiety and depression. The questionnaire consists of 14 questions with a 4-point Likert scale, and two 7-item subscales for anxiety and depression.

##### Productivity

The Work Productivity and Activity Impairment questionnaire^31^ will be used to assess productivity and impairments in paid/unpaid work and activities. The questionnaire is self-reported and participants are asked to recall the time missed from work in the last 7 days.

##### Physical activity

Physical activity will be assessed using an ActiGraph wGT3X-BT activity monitor (ActiGraph, Pensacola, Florida). Participants will be asked to place the device on their right anterior hip during waking hours for 1 week prior to attending PR (baseline) and for 1 week prior to their 6-week follow-up visit. Participants will be asked to remove the device for water-based activities and for sleep. Written instructions will be provided to the participants. Full methodology for the assessment of physical activity is provided in online supplemental table 2.

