### Procedure

After receiving a research fact sheet, patients eligible for the study will be asked if they would like to participate after they have had the opportunity to ask questions. If they wish to take part, they will be asked to provide written informed consent (Appendix A). Reasons for declining the study will be taken as field notes. If they wish to participate, they will be asked to provide written informed consent. Reasons for declining to participate will be reflected in the field notes. The staff of the family medicine centres, doctors of the City Tuberculosis Hospital, the City Tuberculosis Dispensary, the National Hospital, District Hospitals and the National Centre of Cardiology and Internal Medicine will screen patients for eligibility and refer interested patients to the PR study team. Interested patients will be screened by the study team to confirm interest in participation and to schedule the baseline visit. After providing written informed consent, participants will undergo a baseline assessment at the NCCIM by a specially trained team of researchers and residents. After the baseline measures are complete, participants will be randomised into one of two groups: PR or usual care control. At 6-week postbaseline and 12-week postbaseline, patients will undergo follow-up assessments. If participants are not able to attend follow-up assessments in person, questionnaires only will be completed via telephone appointment. Experiences of the patients living with PTBLD and PR deliverers will be explored in interviews and focus groups. Participants who drop out of the trial will be asked to take part in an interview and information provided freely by the participants will be collected as field notes. All outcome measures will be performed at 6 and 12 weeks by dedicated staff who are blinded to group allocations. Control participants will be offered PR at the end of the study (see figure 1).

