### Intervention

The PTBLD PR programme will be held two times weekly for a period of 6 weeks. Each session will last approximately 2 hours, consisting of exercise and health education (online supplemental table 1). The PR programme recruitment will be rolling rather than fixed groups, with a maximum capacity of five patients per session (due to pandemic) and supervised by a nurse, doctor, researcher or physiotherapist. The equipment used will be simple and based on local availability. It will be based on the core elements of an evidence-based rehabilitation, including exercises and health education, but we will be adapting the detail and delivery based on the qualitative work in Stage 1.

10.1136/bmjopen-2021-048664.supp1Supplementary data

Core components of PR exercise are upper and lower body resistance training and aerobic training will be informed by international guidelines.^11 20^ The strength exercises will include (at least) bicep curls, pull-ups, sit-to-stands and step ups. Patients will be asked to do one session of strength training and to walk every day at home in addition to structured classes. Minimal equipment will be used where possible, such as bottles filled with water, to achieve the desired weight in kilograms and to offer insight into how participants can exercise effectively at home during and after finishing PR. Aerobic exercise will include walking and static cycling. Walking will be individually prescribed at a speed equivalent to 85% maximal oxygen capacity (VO_2_) peak derived from the ISWT.^21 22^ Walking will be monitored and target duration increased by the instructor as the programme progresses. The content delivered within the education sessions will be based on existing materials, with refinement from stage 1 of this trial and will be delivered by an interdisciplinary team.

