### Randomisation

Randomisation will occur through a web-based service Sealed Envelope and conducted in a designated room by a dedicated member of the research team. Participants will be randomised (1:1) to either PR or usual care. A dedicated member of the research team will inform the assessors of group allocations via telephone. Participants will be informed at the end of their baseline visit to arrange their first PR class.

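### The second activity-monitor week falls inside the PR programme, so classes enter one arm's record only, and the article does not settle when the first (baseline) week is worn

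*Protocol article*

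**What the plan says.** All references are to the Protocol article.

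- **Wear weeks** (Physical activity): the device is worn "for 1 week prior to attending PR (baseline) and for 1 week prior to their 6-week follow-up visit". The only stated reasons to take it off are water and sleep. The full method is referred to online supplemental table 2, which is not shown.
- **Schedule** (Outcomes, Table 1): activity monitoring is marked at baseline and 6 weeks, and not at 12 weeks.
- **Visits** (Procedure): "At 6-week postbaseline and 12-week postbaseline, patients will undergo follow-up assessments".
- **Programme** (Intervention): "The PTBLD PR programme will be held two times weekly for a period of 6 weeks", and "Each session will last approximately 2 hours, consisting of exercise and health education".
- **Order of baseline and randomisation** (Procedure): "After the baseline measures are complete, participants will be randomised into one of two groups: PR or usual care control".
- **Disclosure of the arm** (Randomisation): "Participants will be informed at the end of their baseline visit to arrange their first PR class".
- **Controls** (Procedure): "Control participants will be offered PR at the end of the study".

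**The concern.** **Follow-up week.** The visit comes 6 weeks after baseline and the programme lasts 6 weeks, so the week before the visit is a week of classes. Only the PR arm has classes. Its record then contains the supervised intervention, while the control record does not. A gap between the arms could arise purely because one arm came to class, with no change in what participants do on their own. No later wear week could separate the two explanations.

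**Baseline week.** The week is called baseline, but it is defined by an event that controls do not have while they are in the trial. The sections on procedure, randomisation and physical activity also leave it open whether the week precedes randomisation or follows disclosure of the arm. If it follows disclosure, knowing the arm could alter activity during the week. Any analysis that uses that value as a starting point would then inherit the effect.

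**Working it through.** The article gives no figure to reproduce here. The check is a day count.

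**Inputs from the article:** baseline visit = day 0; 6-week visit = day 6 × 7 = 42; second wear week = the 7 days before it, days 35 to 41; classes = 2 × 6 = 12; class length about 2 hours.

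**Assumed, because the article does not state them:** day *s* of the first class; *g* days between the two classes of a week; full attendance.

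**Step 1. Can the programme end before the wear week?** Class days are *s* + 7*w* and *s* + *g* + 7*w*, for *w* = 0 to 5. The last class is on day *s* + 35 + *g*. With *s* at or after day 0, this is always later than day 34, so the programme cannot end before the window opens.

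**Step 2. How many classes fall in the window?** Days 35 to 41 are one full week, so each of the two weekly series meets it once. A count over *s* = 0, 1, 3, 7, 8, 14, 21 and *g* = 2, 3, 4 (21 combinations) gave exactly 2 classes every time.

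| First class | Last class (*g* = 2 to 4) | Classes in days 35–41 | Classes on or after day 42 |
|---|---|---|---|
| day 0 | 37–39 | 2 | 0 |
| day 1 | 38–40 | 2 | 0 |
| day 7 | 44–46 | 2 | 2 |
| day 14 | 51–53 | 2 | 4 |

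The day 7 row is the case in which a full wear week sits between the baseline visit and the first class. Two classes are then still to come at the 6-week visit.

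**Step 3. Would calling the visit post-PR, as the Blinding section does, help?** For the 7 days before the visit to hold no class, the visit must be at least 8 days after the last one. With the earliest start and *g* = 3, the last class is on day 38 and the visit could not be before day 38 + 8 = 46, against day 42.

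**Step 4. How much time is involved?**
- Session time: 2 × 2 h = 4 h in the wear week.
- Share of wear time, if the device is worn 10 to 16 hours a day (assumed): 4 / (7 × 10) = 5.7% down to 4 / (7 × 16) = 3.6%.
- Exercise time, if a class holds 30, 60 or 90 minutes of exercise (assumed, the rest being education): 2 × 30 / 7 = 8.6, 2 × 60 / 7 = 17.1 and 2 × 90 / 7 = 25.7 minutes a day.

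The share of higher-intensity activity cannot be computed from the article.

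**Step 5. When is the baseline week worn?** No arithmetic applies, so the statements are set side by side.
- *Before randomisation:* the Procedure section completes baseline measures first, Table 1 lists monitoring under baseline, and the Physical activity section labels the week as baseline.
- *After disclosure:* the Randomisation section informs participants when the baseline visit ends, so that they can book the first class. A week worn just before that class can therefore fall after disclosure. The Procedure section mentions no run-in week or earlier visit at which a device is handed out.
- *Controls:* they are offered PR only when the study is over, so the stated anchor gives them no week within the trial.

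The text permits both orders and does not say when the device is issued.

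**The case against.** **A reader might infer that the baseline week is definitely recorded after the arm is known.** The article does not support that. Its one explicit statement of order puts baseline measures before randomisation, and a week worn before randomisation is also a week before PR. What stands is that the sections do not agree and that the stated anchor cannot serve controls. A baseline measurement is plainly intended for everyone, so for controls this is a faulty definition and not an omitted measurement.

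**A reader might also infer that classes are certainly counted as activity.** Supplemental table 2 may exclude or flag class time, and leaving such detail to a supplement is no fault. However, the wear weeks are fixed in the article itself. A processing rule could remove class time, but it would not create a week after the programme.

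**Total activity is a legitimate outcome.** The article does not say that its target is activity outside class, and daily home walking is part of the intervention. This stands: measuring during the programme is not wrong in itself. The limit is on interpretation.

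**Bias through the baseline value presupposes an analysis that uses it.** The Data analysis section names mixed models and covariate adjustment for the ISWT only. A plain comparison of arms at 6 weeks would not use the baseline week. This stands, so the bias is conditional.

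**The minutes per day are assumed.** They also suppose that every exercise minute registers on a hip-worn device, although classes include static cycling and strength work, and that class displaces no other activity. This stands: the figure is illustrative.

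**Conclusion.** The follow-up part holds on the stated timings. With a regular two-a-week programme begun at or soon after the baseline visit, about two classes (about 4 hours) fall in the PR arm's second wear week and none in the controls', and activity after PR is never monitored. Unless supplemental table 2 already handles this, a between-arm difference in total activity cannot be taken as a change in daily activity. The 9 to 26 minutes a day shows the possible scale under an assumed 30 to 90 minutes of exercise per class; it is not an estimate of the bias.

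The baseline part holds as an inconsistency: the Procedure, Randomisation and Physical activity sections must be reconciled, and the week needs a definition that fits both arms. That it is in fact worn after disclosure is not established.

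The matter is worth correcting but confined to a secondary outcome. The monitor weeks do not affect the primary ISWT analysis.

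**What to change.** 1. **Baseline week.** Anchor it to the same event before randomisation in both arms, for example by issuing the device at consent, and disclose the arm only once the week is complete. Align the Procedure, Randomisation and Physical activity sections with this, and say from which day the 6 weeks to the follow-up visit are counted. *Cost:* about a week's delay before the arm is known, and one device return or telephone call.

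2. **Follow-up week.** Log the date and time of every class. Report activity excluding class time, or on non-class days in both arms, beside total activity. State beforehand which of the two supports a claim about daily activity. *Cost:* slightly more processing.

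If supplemental table 2 already contains either element, it is enough to state it in the main text; otherwise the table should be updated to match.

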### Cost/benefit analysis

The cost of the PR programme will be calculated, including single and recurrent costs. Single costs will include the necessary costs to set up and run PR, and the recurrent costs will include any item with a life expectancy of no more than 1 year, for example, disposable materials. Fixed costs will be captured before the first patient being recruited into the trial. Recurrent costs will be collected at the halfway stage of recruitment. An average cost of PR per patient will be calculated.

### Data management

Data collected during the study will be entered onto a database using Research Electronic Data Capture,^32 33^ hosted by University of Leicester, UK. Access to the database will be via a secure password-protected web interface. Data will be validated using real-time data entry validation and electronic checks, led by the Independent Data Monitoring Committee (IDMC) at the University of Leicester, UK. The participants will be allocated a unique study-specific identification code.

### Data analysis

For stages 1 and 2b, qualitative data will be transcribed verbatim in Russian and translated into English for triangulation with UK-based researchers. Transcripts will be analysed using thematic analysis; following the six distinct stages of familiarisation with data; generating initial codes; searching for themes; reviewing themes; defining and naming themes and producing the report.^34 35^ The qualitative lead will carry out initial coding and a sample of the transcripts will be coded independently by a second researcher to improve consistency and interpretive authenticity. The team will meet regularly to review emerging themes, with close attention to interactions within the interview and focus group data.

For stage 2a, quantitative analysis will be conducted using Statistical Package for the Social Sciences. Data will be reported as mean (SD), median (IQR) or frequency (%) as appropriate. All randomised patients will be included in an intention to treat analysis with the primary efficacy analysis based on both per protocol and modified intention-to-treat populations, with missing data imputed. For the primary analysis, the differences in the primary outcome of walking distance on the ISWT will be estimated using mixed models (unadjusted and adjusted for covariates if there are differences between groups at baseline). There will be no formal interim analysis of the data.

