Explore the views of people living with PTBLD and HCPs (referrers and deliverers) involved in the care of patients living with PTBLD to inform the adaptations needed for a PR programme suitable for people living with PTBLD in Kyrgyzstan.Conduct a single-blind fully powered RCT to assess the effectiveness of adapted 6-week PR on maximal exercise capacity (assessed by the incremental shuttle walking test (ISWT)).Evaluate a range of secondary outcome measures including health-related quality of life, respiratory symptoms, functional status and psychological well-being following PR.Assess any further changes in all outcome measurements 12 weeks postbaseline.Assess the acceptability of PR of participants and the staff delivering PR to inform further improvements to the service.

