#### Stage 2a

Assuming a statistical significance level of 5% and a statistical power of 80%, in order to detect a 35 m difference in ISWT measured at baseline and after completion of PR,^23^ a total of 114 participants are required (PR: 57 participants or waiting list control: 57 participants). This power calculation was performed using a paired t test and assumes the ISWT follows an approximately normal distribution. Data from a feasibility study in Uganda, assessing PR in a PTBLD population, have guided this calculation.^14^ Conservatively assuming up to 30% loss to follow-up at 6 weeks, this will require up to 114 participants to be recruited and randomised (1:1) to each arm. The estimated 70% ineligibility rate suggests approximately 543 patients with PTBLD will be screened for this trial.

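### Two undefined populations, per protocol and modified ITT, are both made primary, with no decision rule and with the all-randomised ITT analysis left out of the primary role

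*Protocol article*

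**What the plan says.** The Data analysis section of the protocol article names three populations in one sentence. It opens with everyone: "All randomised patients will be included in an intention to treat analysis". It then has the "primary efficacy analysis based on both per protocol and modified intention-to-treat populations, with missing data imputed". The per-protocol and modified ITT sets therefore share the primary role, and the all-randomised set does not have it. The section defines neither of the two, does not rank them, and does not say whether one or both must show a benefit. No other section names a single primary population.

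The next sentence says that differences in ISWT distance will be "estimated using mixed models (unadjusted and adjusted for covariates if there are differences between groups at baseline".

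The purpose is given in the list of objectives: "Conduct a single-blind fully powered RCT to assess the effectiveness of adapted 6-week PR on maximal exercise capacity". The sample size section sets the target, "in order to detect a 35 m difference in ISWT measured at baseline and after completion of PR", at 5% significance and 80% power. No non-inferiority or equivalence margin appears anywhere.

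**The concern.** A primary analysis should give one answer. Here the plan can return two, and if they differ it does not say which is the result of the trial. That leaves room for the more favourable one to become the headline.

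A per-protocol set is conventionally given co-primary standing in non-inferiority trials, where ITT can make the arms look falsely alike. With no margin, this is by implication a superiority comparison, and that reason is absent.

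The arms also differ in what can be failed. Rehabilitation means two supervised sessions a week for 6 weeks plus home exercise. Usual care is existing medication and a booklet. If per protocol means enough attendance, exclusions can fall only on the rehabilitation arm, and attenders would be compared with largely unselected controls. The protocol allows for up to 30% loss to follow-up at 6 weeks, so the number excluded need not be small.

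**Working it through.** **The plan's own figure.** The sample size section says "a total of 114 participants are required (PR: 57 participants or waiting list control: 57 participants" and "This power calculation was performed using a paired t test". It states no SD, so 57 per arm cannot be reproduced, only solved backwards (two-sided 5% assumed, 80% power, 35 m):
- Two-sample: SD = 35 / [(1.960 + 0.842) × √(2/57)] = 66.7 m (66.1 m with the exact t distribution).
- Paired: SD = 35 × √57 / (1.960 + 0.842) = 94.3 m (92.7 m with the exact t distribution).

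I use 66-93 m as the range. Whether 114 is a total or a number per arm is a separate question. The figures below take 57 per arm.

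**A. Two primary populations, no selection.** Assume that per protocol is a random fraction f of the modified ITT set with the same true effect. The two test statistics then correlate √f. The modified ITT test has mean 1.960 + 0.842 = 2.802 under the alternative, and the per-protocol test has mean 2.802 × √f. Bivariate normal results:

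| f | correlation | type I error, either may succeed | per-protocol power | power, both must succeed |
|---|---|---|---|---|
| 0.5 | 0.707 | 8.3% | 51% | 49% |
| 0.7 | 0.837 | 7.6% | 65% | 63% |
| 0.9 | 0.949 | 6.5% | 76% | 74% |

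The upper bound for two independent tests is 1 - 0.95² = 9.75%. If both must succeed, type I error does not rise; it falls to 1.7-3.5%.

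**B. Selection in the rehabilitation arm only, no true effect.** Assume 30% of that arm is excluded and adherence correlates 0.3 with the ISWT outcome.
- The mean of the retained 70% of a standard normal is φ(z at 0.30)/0.70 = 0.348/0.70 = 0.497.
- Shift in the rehabilitation mean: 0.3 × 0.497 = 0.149 SD, which is 9.8 m at SD 66 m and 13.9 m at SD 93 m, or 28-40% of the 35 m target.
- Standard error: √(1/57 + 1/39.9) = 0.206 SD. Standardised shift: 0.149/0.206 = 0.72.
- Unadjusted type I error: 1 - Φ(1.96 - 0.72) + Φ(-1.96 - 0.72) = about 11%.

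With correlations of 0.1-0.3 and 60-80% retained, the shift runs from about 2 to 13 m at SD 66.7 m (3 to 18 m at SD 93 m), and the unadjusted type I error from 5.4% to 14.5%.

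**C. The same test adjusted for baseline ISWT.** Assume a baseline-outcome correlation r of 0.6 or 0.8, so the residual SD is √(1 - r²) = 0.8 or 0.6. The result depends on what adherence is related to:
- Baseline fitness only (correlation 0.3 with baseline): adjustment removes the shift, and type I error is about 5%.
- The outcome as a whole, including its baseline part: the shift becomes 0.149 × (1 - r²), and the standardised shift is 0.149 × √(1 - r²)/0.206 = 0.58 or 0.43, giving about 9% or 7%.
- The outcome but not baseline: the shift stays at 0.149, and the standardised shift is 0.149/(0.206 × √(1 - r²)) = 0.90 or 1.20, giving about 15% or 22%.

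A simulation under these assumptions (57 per arm, 6,000 replicates, t-test and ANCOVA standing in for the mixed models) agrees to within about one percentage point.

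**The case against.** The strongest defence is that per protocol is undefined here and its definition may lie in a fuller protocol or analysis plan. It might exclude controls too, for eligibility violations or missed assessments. This stands in part. A reader might infer that the per-protocol result is biased towards rehabilitation. The document supports only that it is open to selection bias; direction and size cannot be known from it. A later definition would not cure the point, however, because the article itself makes both sets primary.

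It can also be said that relying on both populations may mean that both must agree, which does not inflate error. That reading is as available as the other, and its price is power. Neither reading keeps the planned 5% and 80% together.

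Three further inferences go too far:
- **Four primary analyses.** Two populations times unadjusted and adjusted models gives four only as a maximum. Adjustment is conditional on baseline differences and no covariates are named, so an error rate for any of four tests mixes in a separate issue.
- **One error rate for the adjusted per-protocol test.** The 0.15 SD shift and the 11% error belong together only for the unadjusted contrast. After adjustment the error depends on the mechanism.
- **Modified ITT contradicts imputation or the all-randomised analysis.** Participants can be removed for ineligibility found after randomisation while missing outcomes are imputed for the rest, and the all-randomised analysis can be run separately.

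**Conclusion.** The point holds. The protocol article gives primary status to two populations that it does not define, provides no rule for disagreement, and leaves the all-randomised analysis outside the primary role. This is a stated choice, not a detail left to an analysis plan, and it bears on the headline result of a trial presented as fully powered.

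The sizes in the working are illustrations. Those for two populations assume random exclusion and a common effect. Those for selection assume attendance-based exclusion in the rehabilitation arm and a chosen correlation. At a correlation of 0.1 the bias in a single unadjusted test is slight (type I error 5.4-6.0%). What needs no assumption is that the plan has no single primary answer. It must be settled before outcome data are seen.

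**What to change.** Name one primary analysis: all randomised participants, in the arm allocated, for the between-arm difference in ISWT distance at the 6-week post-rehabilitation visit, from one prespecified mixed model. Say that missing ISWT values are handled under missing at random. The model itself or multiple imputation can both do this, and which to use is a matter of preference. Fix the covariates in advance so that there is one model as well as one population.

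Keep per protocol, and a modified ITT if it is wanted. Define each (for per protocol, the minimum attendance and any criterion that applies to controls) and label both supportive. Dropping the modified ITT is optional.

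The cost is wording only: no change to data, visits or sample size. The downside is that the headline estimate may be smaller than the per-protocol one.
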